##### Analysis of moderators

Age, sex, education and score on MoCA, four variables considered as time-invariant for the duration of the study, will be assessed as potential moderators of the impact of training on primary and secondary outcomes. Prior to their use, we will verify that they are independent from each other with a chi-squared test or correlations.

### Adherence sub-study

#### Design

The adherence sub-study will be a pragmatic quasi-experimental study including all participants from the Swiss and Canadian sites (about 96). Following the 26-week efficacy trial, participants in the experimental group will be asked to continue to use the StayFitLonger programme with no supervision and will be invited to a refresher course to answer questions and discuss potential issues that occurred during the RCT. Participants in the control group will cross-over to use the experimental programme for 22 weeks (Table 1).

#### Variables

*Adherence.* For the entire duration of the study (between T0 and T1, and T1 and T2), three measures of adherence in relation to the device usage will be recorded directly from the application (Table 3): dose measured by the time (min) spent on the programme per week; volume corresponding to the total number of repetitions performed per week within each activity (e.g., 3 quizzes completed while using the Quiz activity); and frequency corresponding to the number of sessions per week. These will be recorded separately for the physical and cognitive activities. Adherence will be calculated for each individual by plotting weekly data over the entire training period.

**Table 3 Tab3:** List of variables measured during the adherence sub-study

Adherence sub-study variables		Timepoints		
***Domain***	***Variable***	T0	T1	T2
Adherence	Dose variable: total time of training for each activity	During training		
	Volume variable: number of times each activity is carried out			
	Frequency variable: number of training sessions of at least 30 min performed per month			
User experience	Ad-hoc questionnaire exploring the quality of the introductory course	X		
	AttrakDiff 2 scale		X	X
Acceptability	Ad-hoc questionnaire to obtain ratings on different components (enjoyment, appropriateness, safety, self-evaluation)		X	X
Usability	Ad-hoc questionnaire exploring the impact of unique features of the programme (virtual coach, social interactions, preference, gamification, educative content, self-management, usability)			X

*User experience.* The AttrakDiff 2 scale [78] will evaluate user experience (Table 3) with a 28-item questionnaire given at T1 and T2. It will measure attractiveness, pragmatic quality and hedonic qualities (stimulation and identity) of the application. Pragmatic quality corresponds to usability for instance efficiency, effectiveness and learnability. Hedonic qualities refer to the programme’s originality and beauty. In addition, a 9-item questionnaire will be given at T0 to ask participants’ knowledge regarding the effects of cognitive and physical interventions and the quality of the introductory courses.

*Acceptability.* A 9-item ad-hoc questionnaire will be used at T1 and T2 to measure acceptability (Table 3) that is, the participants’ feeling toward the programme (enjoyment, safety, efficacy, motivation to use other programmes) and its appropriateness (for older adults, to improve physical and cognitive health and to maintain a social circle).

*Usability.* A 16-item ad-hoc questionnaire will be used at T2 to measure usability (Table 3). Participants will be asked to rate the virtual coach, social interactions, gamification, educative content, and self-management.

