#### Interventions

##### Introductory courses

Four face-to-face introductory sessions will be provided to familiarise participants with the material and the assigned application (Table 1). Two sessions of 3 h will present how to use the tablet and accessories (e.g., handling, charging), how to navigate in the application and how to complete the cognitive exercises. Two sessions of 2 h will present the physical exercises and teach participants how to place the motion sensor (Physilog®5, GaitUp, Switzerland) that will be used to record bodily measurements. In both programmes, physical activity instructors will ask participants to practice physical exercises for a total of 30 to 45 min distributed over the day. They will be recommended to train using the same physical exercises for at least 3 weeks with three sessions per week and a day of rest between each session. Cognitive training instructors will encourage participants to practice the cognitive exercises at least 3 times per week for 15 min each time. Participants will be made aware that during an ideal training session, activity should be perceived as of moderate difficulty. Instructions on physical and cognitive activities will be provided by a different instructor, the same for both programmes. Instructors will specifically be asked to present and explain the two programmes in similar ways.

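### Adherence frequency is defined in two incompatible ways, and Table 3's 30-minute minimum, if applied to cognitive activities counted on their own, excludes sessions of the recommended 15 minutes

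*Protocol article*

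**What the plan says.** All references are to the protocol article.

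- **Adherence sub-study, Variables (text).** Three measures are taken from the application: dose, volume and frequency, each per week. Frequency is given as "frequency corresponding to the number of sessions per week", with no minimum length. On all three measures the text adds: "These will be recorded separately for the physical and cognitive activities". It then says: "Adherence will be calculated for each individual by plotting weekly data over the entire training period".
- **Adherence sub-study, Table 3.** The corresponding row reads: "Frequency variable: number of training sessions of at least 30 min performed per month". The dose and volume rows are worded per activity and state neither a threshold nor a time unit.
- **Interventions, Introductory courses.** Participants are encouraged to "practice the cognitive exercises at least 3 times per week for 15 min each time". For the physical part they are asked to "practice physical exercises for a total of 30 to 45 min distributed over the day", with three sessions a week separated by rest days.
- **Adherence sub-study, Statistical analyses.** Dose, frequency and volume are each modelled over time by polynomial regression. Cumulative adherence values are regressed on personal characteristics and allocated group. Change scores on the efficacy measures are correlated with adherence. A separate yes/no classification asks whether a participant keeps up the recommended dose.

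**The concern.** The two definitions cannot be converted into one another. Going from weeks to months would be a mere change of unit if the same sessions were counted, but they are not: one rule counts every session and the other only those of 30 minutes or more. Moving between them requires the length of each session.

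The 30-minute minimum also sits badly with the trial's own training advice, since it is twice the recommended length of a cognitive session. With cognitive activities counted separately, as the text specifies, the variable would then miss the behaviour it is meant to record.

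Adherence is one of the study's two main objectives, and frequency is one of its three measures. With both definitions in print, either could be adopted after the application logs have been seen and still be called the planned one.

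**Working it through.** The plan gives no figure to reproduce, so the check sets the definitions side by side and counts sessions under each.

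**Inputs**

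- Text rule: all sessions, per week, by activity type (Variables).
- Table 3 rule: sessions of at least 30 min, per month (Table 3).
- Recommended cognitive practice: at least 3 sessions a week of 15 min (Introductory courses).
- Recommended physical practice: 30 to 45 min in total over the day, 3 sessions a week with a rest day between (Introductory courses).
- Duration: 26 weeks of trial plus 22 weeks of sub-study = 48 weeks.
- Weeks per month: 52/12 = 4.33.

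**Step 1: cognitive activities, participant following the recommendation exactly**

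| Period | Text rule | Table 3 rule |
|---|---|---|
| Per month | 3 × 52/12 = 13 | 0 |
| 26 weeks | 3 × 26 = 78 | 0 |
| 48 weeks | 3 × 48 = 144 | 0 |

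The Table 3 column is zero because 15 min < 30 min for every session. Training more often at 15 minutes raises the text count and leaves the Table 3 count at 0. Sessions that run to 30 minutes or more would count under both.

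**Step 2: physical activities**

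The result depends on what a session is, which the article does not define.

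- If a session is a training day, the recommended total is 30 to 45 min, which meets the threshold. The count is about 13 a month under both rules.
- If a session is a single sitting, practice split over the day can fail. Two equal halves last 30/2 = 15 to 45/2 = 22.5 min, and neither counts under Table 3.

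**Step 3: time unit and the planned trajectories**

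Weekly data give 48 points per participant over the whole study. A monthly variable gives about 48/4.33 = 11. The monthly definition therefore cannot supply the weekly plots that the text calls for.

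**Step 4: which analyses use the variable**

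- Affected: the frequency trajectories, the regression of cumulative frequency on personal characteristics and group, and the correlation of frequency with change scores.
- Not affected: the mixed-model analysis of the Timed-Up & Go and the secondary outcomes, the dose and volume measures, and the yes/no classification, which rests on dose.

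**The case against.** The strongest reply is that the zero is not inevitable. The Table 3 frequency row, unlike the dose and volume rows, does not refer to each activity. It could mean a programme-level session in which 30 to 45 min of physical and 15 min of cognitive practice are added together (45 to 60 min) and pass the threshold. That reading is possible, so the zero has to be stated as conditional on separate counting. It conflicts, however, with the text's statement that the measures are recorded separately, and even if adopted it leaves the unit and the threshold in contradiction.

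A second reply is that the text is evidently the operative version: all three measures are weekly there and weekly plotting follows, so Table 3 is simply the line to correct. This stands as a guide to the remedy. It does not make the difference clerical, because the 30-minute minimum is a substantive counting rule that appears nowhere in the text.

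Three stronger readings are tempting, and the document does not support them:

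- *Compliant participants would be classed as non-adherent.* The only such classification uses the recommended dose, not frequency, and dose carries no 30-minute filter.
- *Conclusions about who adheres would be reversed.* The calculation concerns one hypothetical participant. Nothing shows that the sign of any regression coefficient would change.
- *The physical count would run from 0 to 13 a month for the same behaviour.* This needs a session to mean one sitting. The advice on three sessions a week with rest days between them treats a session as a training day, so the loss is a possibility only.

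**Conclusion.** The contradiction is real and explicit within one section: a weekly count of all sessions against a monthly count of sessions of at least 30 minutes. For a participant following the cognitive advice exactly, the difference is about 13 sessions a month against 0, or 144 against 0 over 48 weeks.

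Those figures assume that Table 3's threshold is applied to cognitive activities on their own, that sessions last the recommended 15 minutes, and that a month has 52/12 weeks. For physical practice, a loss arises only if sessions are counted per sitting and the practice is split.

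The consequence is possible material distortion of the frequency analyses listed in step 4. Because it is confined to one of three adherence measures in the sub-study and does not reach the efficacy analyses, the severity is moderate. It should be corrected before analysis.

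**What to change.** Before the adherence data are analysed, replace the frequency row of Table 3 so that it matches the text: number of sessions per week, counted separately for physical and for cognitive activities, with no 30-minute minimum. Add one definition: a session is a calendar day with logged activity of that type. Practice split over the day then counts once, which agrees with the way the physical advice uses the word.

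The price of this definition is that a second cognitive session on the same day is not counted and a very short one is. The dose and volume measures, analysed alongside, carry that information.

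The cost is one table row and one derivation rule. The application already records use, so no new data are needed, and the training recommendations themselves are not touched.

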#### Statistical analyses

Dose, frequency and volume variables will be analysed with polynomial regression models including linear and non-linear trajectories. This will allow to establish the best fitting model describing the use of the programme over time. Regression analyses will examine whether the cumulative values on adherence variables are predicted by personal characteristics, and the group to which they were assigned. We will also examine adherence dichotomously by classifying participants as a function of whether they maintain or not the recommended dose of the programme over time. Finally, we will evaluate whether change scores on primary and secondary measures of efficacy are correlated with adherence.

Qualitative analyses will be used to characterize usability, acceptability and user experience. In addition, correlations analyses between these parameters and a series of variables (age, sex, education, cognitive profile, participant’s technology and gaming profile) will be performed.

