## Objectives and hypotheses

The StayFitLonger study has two major objectives that will be addressed in the trial and the sub study. The **efficacy trial** will test the effect of the training on physical, cognitive, affective, and psychosocial outcomes using a 26-week double-blind parallel-group randomised control trial (RCT). Participants will be allocated randomly to either the StayFitLonger training home-based computerised programme (experimental intervention) or a home-based computerised comparator (active control). The primary objective is to assess whether the StayFitLonger programme leads to larger pre-post improvement than the active control condition on the Timed-Up & Go (TUG), a broadly used and validated functional physical task to measure lower extremity function, mobility and balance. Participants allocated to the experimental intervention are expected to show larger post-training improvement on the TUG than participants in the control intervention. As a secondary objective, we will assess whether the StayFitLonger programme improves physical, cognitive, affective, and psychosocial secondary outcomes. We will also explore whether gains differs in robust vs. pre-frail seniors since some studies suggest that changes in response to training might depend on frailty status [11, 14].

The **adherence sub-study** will rely on a pragmatic quasi-experimental design. At the end of the 26-week RCT, participants in the experimental group will be asked to continue using the programme and participants in the control group will ‘cross-over’ to the StayFitLonger programme. This sub-study will last 22 weeks and indicators of adherence will be recorded throughout the entire duration of the StayFitLonger study (48 weeks). This will allow us to assess whether adherence is maintained over time and whether it is influenced by personal characteristics, the presence or not of supervision and the type of intervention. Usability, acceptability and user experience will also be evaluated.

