#### Study population

One hundred and twenty-eight French-speaking healthy participants will be recruited, 64 in Switzerland, 32 in Canada and 32 in Belgium. Participants will be community-dwelling older adults. They will be recruited through diverse sources including ads, newsletters, social media, and flyer distribution during various events. Recruitment will be carried out with the help of two community associations, Pro Senectute in Switzerland and Brusano in Belgium, and from the bank of participants of the IUGM research centre in Canada.

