##### Analysis of efficacy on primary and secondary outcomes

All statistical tests will be two-tailed and a *p* value < .05 will indicate statistical significance. Effect sizes will also be assessed. Standard descriptive statistics will be provided with means and standard deviation for demographics and baseline characteristics. Group comparisons will be made using t-tests for continuous variables and chi-square analyses for discrete variables.

The primary efficacy analysis will be done with a modified intention-to treat (mITT) approach. All participants will be included in the analyses and the characteristics of those who withdrew will be analysed, as well as the causes leading them to leave the study. A linear mixed model will be used to analyse the data, as it handles correlated data and unbalanced designs and are robust against missing values. The fixed effects will be Intervention (StayFitLonger vs. active control), Time (T0, T1) and their interaction. If the StayFitLonger training is more beneficial than the active control training, a significant interaction will be expected. In such case, the presence of a significant difference between T0 and T1 in each group will be evaluated, as well as group difference on change scores at post-training using the pre-training and control group as reference points. The same analysis will be used with primary and secondary outcomes. To examine the effect of frailty status on efficacy, participants will be stratified into robust and pre-frail seniors and data will be analyzed separately in these two populations using the same method described above.

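### The adherence trajectories are assigned to polynomial regression with no allowance for repeated weekly values within a person, so an ordinary fit would have the wrong error term

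*Protocol article*

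**What the plan says.** All references are to the protocol article.

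- **Question.** Objectives and hypotheses, on recording adherence through both study periods: "This will allow us to assess whether adherence is maintained over time and whether it is influenced by personal characteristics".
- **Data.** Adherence sub-study, Variables, defines dose, volume and frequency per week, recorded by the application and separately for physical and cognitive activities. It adds: "Adherence will be calculated for each individual by plotting weekly data over the entire training period". Adherence sub-study, Design, limits the sub-study to the Swiss and Canadian sites.
- **Model.** Adherence sub-study, Statistical analyses: "Dose, frequency and volume variables will be analysed with polynomial regression models including linear and non-linear trajectories". The stated purpose is to find the curve that best describes use over time. No random effect, clustering or residual covariance is named.
- **Other adherence analyses, same section.** Regressions of cumulative adherence values on personal characteristics and group, and a yes/no classification of each participant by whether the recommended dose is kept up.
- **Contrast.** Efficacy trial, Analysis of efficacy on primary and secondary outcomes: "A linear mixed model will be used to analyse the data, as it handles correlated data and unbalanced designs". That model covers two time points per person.

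**The concern.** Whether older adults keep using the programme is a question about people, so the sampling unit is the participant. Ordinary polynomial regression, on pooled person-weeks or on the curve of weekly means, takes its standard error and its fit criterion from week-to-week scatter as if the weekly values were independent. Two features of usage data break that assumption in opposite directions:

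- Stable differences in level between people inflate the residual variance and make a pooled test of trend too cautious, so a real decline can be missed.
- Differences in slope between people, or carry-over from week to week, make the test too liberal, so a trend can appear that reflects only who was enrolled.

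The article itself gives reason to expect slope differences. It plans to separate participants who keep up the recommended dose from those who do not, and it asks whether personal characteristics, supervision and type of intervention influence adherence. At stake is the description of adherence over time, which belongs to one of the study's two major objectives. The primary TUG analysis is not touched.

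**Working it through.** **Inputs from the article.** Recruitment is "64 in Switzerland, 32 in Canada and 32 in Belgium", so the sub-study has 64 + 32 = 96 people. Duration is 26 + 22 = 48 weeks. That gives up to 96 × 48 = 4,608 person-weeks per variable. The article states no error rate, power or variance for the adherence trend, so there is no planned figure to reproduce.

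**Assumptions.** The mean is flat, total variance is 1 and there is no dropout. The share of variance from level differences (ICC) is 0 to 0.7, the share from slope differences (s) is 0 to 0.20, and the lag-1 autocorrelation (ρ) is 0 to 0.7. The test is two-sided at 0.05, a level the article states for efficacy and which is borrowed here.

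**Formula for the pooled linear slope, ρ = 0.** With complete data the pooled slope equals the mean of the per-person slopes. Let S be the sum of squared centred weeks, n = 96 and T = 48.

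- True variance × nS = T·s + (1 − ICC − s)
- Variance that pooled regression reports × nS ≈ 1
- Ratio R = 1 − ICC + 47s
- Rejection rate under a flat mean = 2·[1 − Φ(1.96/√R)]

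| ICC | s | R | Formula | Simulated (2,000 trials) |
|---|---|---|---|---|
| 0 | 0 | 1.00 | 5.0% | 5.2% |
| 0.3 | 0 | 0.70 | 1.9% | 1.2% |
| 0.5 | 0 | 0.50 | 0.6% | 0.8% |
| 0.7 | 0 | 0.30 | 0.03% | 0.1% |
| 0.5 | 0.01 | 0.97 | 4.7% | 4.8% |
| 0.5 | 0.03 | 1.91 | 15.6% | 15.7% |
| 0.5 | 0.05 | 2.85 | 24.6% | 23.6% |
| 0.5 | 0.10 | 5.20 | 39.0% | 39.2% |
| 0.5 | 0.20 | 9.90 | 53.3% | 52.0% |

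The two errors cancel when 47s = ICC. At ICC 0.5 that is s = 0.5/47, about 1.1% of total variance.

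**Autocorrelation (simulated, ICC 0.5, no slope differences).** The pooled linear test rejects in 4.0%, 11.1% and 21.5% of trials at ρ = 0.3, 0.5 and 0.7. With slope differences and autocorrelation together, the rate is 27% to 55%.

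**Choice of degree (0 to 3, flat mean).** AIC picks a non-flat curve in 1.6% to 72% of trials, against 23% when the data really are independent. BIC does so in 0% to 37%.

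**Fitting the 48 weekly means.** The rate is about 5% with level differences only, and 15% to 72% with slope differences or autocorrelation.

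**On a minutes scale (800 trials per setting, quadratic fit, linear term tested).** Assumed SDs are 30 to 50 min/week for level and 40 to 50 for the weekly residual, with ρ 0 to 0.5.

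| SD between people of 48-week change | Pooled | Weekly means |
|---|---|---|
| 30 min/week | 9–12% | 27–31% |
| 60 min/week | 33–40% | 50–59% |
| 100 min/week | 48% | 65% |

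**Participant as the unit.** A one-sample t-test on per-person slopes rejects in 4.2% to 6.0% of trials in every setting of the 2,000-trial simulation. A polynomial mixed model serves the same purpose but was not simulated.

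**The case against.** The strongest reply is that the article never says person-weeks are pooled or treated as independent. Polynomial terms can be fitted per person or inside a mixed model, and the sentence on plotting each individual's weekly data points towards person-level curves. The stated purpose is descriptive, with no null hypothesis or trend test. Maintenance is also addressed by classifying each participant, which uses one value per person. The article condenses a fuller plan, and covariance structure is often left there.

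Much of this stands. A reader might infer that the plan does treat weeks as independent and will therefore report false trends in 10% to 50% of trials. The documents do not support that: pooling and the 0.05 test are inferences, and with level differences only the error runs the other way. The classification and the cumulative-value regressions are sound on this point.

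Two parts do not stand. First, the article names a correlation-aware method for two time points and a different method for up to 48, so the issue is a stated choice and not only an omitted detail. Nor does it say how individual curves would be combined into an answer for the group. Second, a descriptive aim does not remove the problem, because selecting the best-fitting degree depends on the error term too.

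It can also be said that SDs of 60 to 100 min/week look large beside the encouraged minimum of 3 × 15 = 45 min/week of cognitive practice. But the rate depends on shares of variance, not on minutes. SDs of 20 to 30 min/week for change, scaled to that dose, still gave 25% to 39%.

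**Conclusion.** The point holds conditionally. The method as named does not account for repeated weekly values within a person. If it is carried out as ordinary polynomial regression, the error term is wrong and the direction depends on variances the documents do not give. For a pooled linear term, the false-trend rate is roughly 10% to 50% when slope differences hold about 3% to 20% of the variance or weekly autocorrelation is about 0.5 or more. It is about 0.1% to 1.2% when people differ only in level. These ranges rest on assumed variances, complete data and a borrowed two-sided 0.05 test; they are not properties of the plan as written. The point is worth correcting because the trajectory bears directly on a major objective, but it leaves the efficacy conclusions and the person-level adherence analyses as they are.

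**What to change.** State that weekly dose, frequency and volume are analysed with a mixed-effects polynomial (growth-curve) model with a random intercept and random slope per participant and autocorrelated weekly residuals. A two-stage analysis, with a trend estimated per person and then summarised across people, is an acceptable alternative. Choose the polynomial degree within that model, and report the mean change over the 48 weeks with a 95% CI based on participants.

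The cost is analysis wording and some analysis time. No new data are needed, and mixed models are already planned for the efficacy outcomes. The drawback is that intervals for the trend may be wider than those from an ordinary fit.
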